**Methods:**

This is a protocol of a triple-blinded, blocked-randomized, parallel-group, placebo-controlled clinical trial designed to determine the effect of *Hafnia alvei* HA4597™ supplementation on weight loss and glycaemic control 1 year after bariatric surgery. Patients of Hospital CUF Tejo, Lisbon, that undergo Roux-en-Y gastric bypass are invited to participate in this study. Men and women between 18 and 65 years old, with a BMI ≥ 35 kg/m^2^ and at least one severe obesity-related comorbidity, or with a BMI ≥ 40 kg/m^2^, and who are willing to take 2 capsules of *Hafnia alvei* HA4597™ probiotic supplements (equivalent to 5 × 10^7^ CFU) *vs*. placebo per day for 90 days are included in this study. Assessments are carried out at baseline, 3, 6, 9, and 12 months after the surgery. Loss of weight in excess and glycated haemoglobin are considered primary outcomes. In addition, changes in other metabolic and inflammatory outcomes, gut microbiota composition and metabolites, as well as gastrointestinal quality of life are also being assessed during the trial.

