### Primary outcomes

The primary outcomes are the differences in the number of subjects that will lose at least 50% of excess weight, as well as the number of subjects that will have glycated haemoglobin levels lower than 5.7%, between the probiotic and placebo groups, 1 year after the surgery. The rationale behind the primary outcomes is based on previous studies that have described the effect of *Hafnia alvei* HA4597™. In the preclinical study conducted by Legrand et al. [14], the effect of *Hafnia alvei* HA4597™ supplementation was assessed in two models of obesity, in leptin deficiency *ob/ob* mice and high-fat diet (HFD)-fed obese and overweight mice. Results showed that in both models’ body weight gain was significantly lower by the end of the study (50.1% *ob/ob* and 38.1% HFD), as well as fat gain (38.3% *ob/ob* and 51.9% HFD) [14]. In addition, loss of lean mass was 126.8% lower and food intake reduced 20.8% in the *ob/ob* mice [14]. A second trial was conducted by Lucas et al. [11] using a mice model of obesity characterized by a combination of a HFD-fed obese and a genetic *ob/ob* mice which closely represents the hyperphagia and diet-induced obesity in humans (compulsive eating behaviour combined with hypercaloric diet and functional leptin resistance). The authors observed that *Hafnia alvei* HA4597™ supplementation resulted in 58.1% lower body weight gain, decreased food intake and fat mass gain, and increased lean mass preservation, resulting in an improved lean/fat mass ratio [11]. Moreover, *Hafnia alvei* HA4597™ treatment also improved metabolic outcomes, including glycemia. Basal glucose levels decreased by 1.5-fold compared to standard diet HFD-fed controls [11]. Afterwards, the efficacy of *Hafnia alvei* HA4597™ supplementation was tested in humans [15]. A randomized, placebo-controlled, double-blind trial evaluated the effect of this probiotic (5 × 10^7^ CFU of *Hafnia alvei* HA4597™) on 236 overweight men and women that were following a low-calorie diet [15]. After 12 weeks, significantly more subjects (+ 51%) lost at least 4% of their initial weight comparing to placebo [15]. Furthermore, compared to placebo, subjects in the treatment group had a significant reduction in hip circumference and glycemia, and increased feeling of fullness, which was assessed by a visual analogue scale [15].

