## Sample size

Sample size calculations have considered the outcomes: percentage of excess weight loss and fasting blood glucose levels. Based on previous studies with a population similar to this study, the assumed standard deviation was 10.70 for percentage of excess weight loss [37] and 14.00 mg/dL for fasting blood glucose [38]. To detect a difference of 10.48% [39] in excess weight loss and 11.30 mg/dL [40] in fasting glucose between the intervention and placebo group after 1 year of follow-up, it was determined that 44 participants are required to allow for an 80% power and 95% confidence level. Compensating for possible attrition, 30% additional samples will be recruited, representing a total of 58 participants (29 in each arm — probiotic group and placebo group). Considering that Hospital CUF Tejo receives around 80 patients each year to be submitted to bariatric surgery, of these around 70% are Roux-en-Y gastric bypass, assuming that 29% of the subjects will not be eligible to participate [39], it is anticipated that it will take approximately 18 months to recruit this sample size.

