Some prespecified subgroup analysis will be done based on some confounding variables such as age, gender, diagnosis of type 2 diabetes, etc., for detecting heterogeneity in intervention efficacy across the strata of mentioned variables. However, these subsamples will be compared to the main dependent variables at baseline. Potential confounding variables will be evaluated in each model. Regression models will be used to predict which factors at baseline most contribute to excess weight loss 1 year after the surgery.

Differences will be considered statistically significant when *p* < 0.05. Effect sizes (Cohen d test) will also be assessed to decide whether a clinically relevant effect is found (|d|> 0.50 indicates a medium effect size and |d|> 0.80 indicates a large effect size).

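### Two unranked primary outcomes share one p < 0.05 rule with no multiplicity provision; if either alone can support a claim, the chance of a false-positive primary result is up to 9.75%

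*Protocol article*

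**What the plan says.** The abstract puts both outcomes on the same footing: "Loss of weight in excess and glycated haemoglobin are considered primary outcomes". Study objectives gives each its own primary aim. The Primary outcomes section defines them as responder counts compared between arms 1 year after surgery: "The primary outcomes are the differences in the number of subjects that will lose at least 50% of excess weight", together with "the number of subjects that will have glycated haemoglobin levels lower than 5.7"%. None of these places calls one outcome the main one or says that both must succeed.

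The only decision rule is in the Statistical analysis section: "Differences will be considered statistically significant when" p < 0.05. It is not limited to particular outcomes or analyses. The same section assigns the chi-square test to categorical variables.

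The Sample size section works from continuous percentage of excess weight loss and fasting glucose: "it was determined that 44 participants are required to allow for an 80% power and 95% confidence level". It does not say whether the tests are one- or two-sided, and it mentions no allowance for two primary comparisons.

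**The concern.** With two primary outcomes and a 0.05 threshold for each, the trial has two chances of a significant primary result when the probiotic does nothing. If either result would be presented as the trial's positive finding, the error rate of that headline conclusion is above the 5% applied to each test. The number of primary successes needed, and the order in which they count, is best fixed before anyone sees the data. Under the rule as written, a trial that wins on one outcome and loses on the other can be read either way afterwards.

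**Working it through.** **Inputs.** Two primary outcomes (abstract, Study objectives, Primary outcomes). Threshold 0.05 for each (Statistical analysis). Two-sided testing is assumed. The documents give no correlation between the outcomes, so a range is shown.

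**The plan's own figure of 44.** It does not reproduce at the stated 80% power and 95% confidence. The inputs are differences of 10.48 percentage points and 11.30 mg/dL, with "the assumed standard deviation was 10.70 for percentage of excess weight loss" and "14.00 mg/dL for fasting blood glucose". The normal-approximation formula is n per arm = 2(1.960 + 0.842)²/d².
- Excess weight loss: d = 10.48/10.70 = 0.979; 2 × 7.85/0.959 = 16.4, so 17 per arm, 34 in total (36 by t-test).
- Fasting glucose: d = 11.30/14.00 = 0.807; 2 × 7.85/0.651 = 24.1, so 25 per arm, 50 in total (52 by t-test).

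A total of 44 does match excess weight loss at two-sided alpha 0.025 with 80% power by t-test. It also matches alpha 0.05 with 90% power by the normal approximation. At 0.025, however, glucose would need 60 to 62, so the figure is not evidence of a planned alpha split.

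**Chance of at least one significant primary result when neither outcome is affected.**
- Independent tests: 1 − 0.95² = 0.0975.
- Correlated tests: 1 − P(|Z₁| < 1.96 and |Z₂| < 1.96) under a bivariate normal.
- Favouring the probiotic only: 1 − P(Z₁ < 1.96 and Z₂ < 1.96); under independence 1 − 0.975² = 0.0494, against a nominal 0.025.

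| Correlation | Either direction | Favouring probiotic |
|---|---|---|
| 0 | 9.75% | 4.94% |
| 0.3 | 9.51% | 4.76% |
| 0.5 | 9.07% | 4.54% |
| 0.7 | 8.35% | 4.17% |
| 0.9 | 7.04% | 3.52% |

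**Small samples.** The responder outcomes would be tested by chi-square, whose true size differs from 5% in groups this small. Exact enumeration (no continuity correction) used 22 and 29 per arm and independent outcomes, with assumed true rates of 70% to 90% for one outcome and 50% to 80% for the other. The chance of at least one false positive was about 8.9% to 10.0%. At 22 per arm with both rates at 80%, each test has size 0.0515, and 1 − (1 − 0.0515)² = 0.100. The approximation is therefore adequate.

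**After a fix.** A fixed sequence with both tests at 0.05 holds the rate at 5%, because the second test is reached only through the first. Holm holds it at no more than 5%. Holm's strictest step is 0.025. Power at 22 per arm by noncentral t, with noncentrality d × √(22/2), is:
- Continuous excess weight loss: 0.979 × 3.317 = 3.25; 89% at 0.05, 82% at 0.025.
- Fasting glucose: 0.807 × 3.317 = 2.68; 74% at 0.05, 64% at 0.025.

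Neither variable is a primary outcome as defined. Power for the two responder outcomes cannot be computed, because no response rates are assumed.

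**The case against.** Four objections deserve an answer.

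**The article is condensed.** An analysis plan not shown here may hold a multiplicity rule, and the 0.05 sentence can be read as a general convention that such a rule would refine. Silence alone would not be a finding. But the article states a rule and applies it to every difference without exception, alongside details as fine as the normality test and effect-size cut-offs. The objection is to that stated rule. The possibility of an unseen provision remains and limits confidence.

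**The decision rule is inferred.** Nowhere does the article say that either outcome alone makes the trial positive. If both must succeed, there is no inflation. If weight and HbA1c are reported as two separate claims, each keeps its 5% level, and the need to adjust is open to debate. This stands, so the error rate can be stated only conditionally. The 95% confidence level in the Sample size section does not settle it, because it is a planning input and not a promise of family-wise control.

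**The size is easily overstated.** A reader might infer that an ineffective probiotic would be declared effective in nearly 10% of such trials. That does not follow: 9.75% includes results favouring placebo. The rate of false claims for the probiotic is 4.94% under independence and lower with positive correlation. The near-doubling survives at low to moderate correlation, but not that absolute level.

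**Splitting alpha is not shown to be free.** A reader might infer from the 82% for excess weight loss at 0.025 that a split preserves the planned 80% power. The plan's other powered variable falls to 64%, and neither figure describes the responder outcomes. No such reassurance can be given.

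**Conclusion.** The point holds in conditional form. The article fixes two unranked primary outcomes and one blanket threshold, with no order, split or joint-success requirement. If either outcome alone can support an efficacy claim, at least one false-positive primary result has a chance of 9.75% under independence, about 9.1% at correlation 0.5 and 7.0% at 0.9. In the probiotic's favour only, it is up to 4.94% against 2.5%. These figures assume two-sided tests, no effect on either outcome and a non-negative correlation that the documents do not give. The defect should be corrected because it bears on the trial's main conclusion, and the correction is small.

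**What to change.** Before unblinding, add one sentence to the Statistical analysis section. It is best added before the coded groups are first compared, since the p-values are visible from then on. Use the responder definitions in the Primary outcomes section, so that the sentence does not bring in a different endpoint. Either:

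- **Fixed sequence:** compare the proportion with at least 50% excess weight loss at 1 year at two-sided 0.05, and compare the proportion with HbA1c below 5.7% at two-sided 0.05 only if the first is significant; or
- **Holm** across the same two comparisons.

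Treat all remaining p-values as exploratory. If the sponsor intends that both outcomes must succeed, saying so would also settle the matter.

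The sequence above follows the order in which the article lists the outcomes, but the article does not present that order as a priority. The sponsor should confirm it.

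Cost: no additional patients. The fixed sequence takes no power from excess weight loss, but HbA1c is not confirmatory if excess weight loss fails. Holm keeps both outcomes in play at some loss of power, and the text should not claim that 80% is kept for the primary outcomes.

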### Secondary outcomes

As secondary outcomes, the impact of *Hafnia alvei* HA4597™ supplementation will be assessed towards changes in gut microbiota composition, including diversity, richness, and characterization of microbes at phylum, class, order, family, genus, and species level at baseline, and 3, 6, 9, and 12 months. Alterations in the metabolites produced by gut microbiota that have already demonstrated a protective or a deleterious effect in obesity and type 2 diabetes conditions, namely short-chain fatty acids (acetate, propionate and butyrate), trimethylamine N-oxide, indole-3-propionic acid, imidazole propionate [18–21], will also be determined at the same timepoints. Another important gut metabolite that will be assessed is ClpB, which is specifically produced by *Hafnia alvei* strain and is related to its recognized metabolic effect on appetite regulation [22]. Changes in ClpB levels will be determined before (baseline and 3 months) and after the intervention (6, 9, 12 months).

Additionally, the trial will assess the effect of supplementation on inflammatory markers, including calprotectin, zonulin, c-reactive protein, lipopolysaccharides, transforming growth factor-β, monocyte chemoattractant protein-1, interferon gamma, IL-1 β, IL-6, IL-10, and on other important metabolic outcomes, such as fasting glucose, HOMA-IR, HOMA-S, HOMA-B, and c-peptide, total cholesterol, HDL cholesterol, LDL cholesterol, VLDL cholesterol and triacylglycerides, and vitamins and minerals status (iron, calcium, zinc, copper, magnesium, vitamin B6, vitamin B12, 25-hydroxy-vitamin D) on all visits. GLP-1 and GIP will also be determined at all visits. Lastly, gastrointestinal quality of life impact will be assessed at baseline, and 3, 6, 9, and 12 months.

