### Gut microbiota composition and gut metabolites

Genomic DNA will be extracted and purified from faecal samples using NZY Tissue gDNA Isolation Kit (NZY Tech, Lisboa, Portugal), as described by Marques et al. [31]. Whole-metagenome shotgun sequencing will be performed on the Illumina HiSeq3000 platform to characterize gut microbiota composition as previously described [32, 33]. Gut metabolites [short-chain fatty acids (acetate, propionate, and butyrate), trimethylamine N-oxide, indole-3-propionic acid and imidazole propionate] will be evaluated by targeted metabolomics in serum and faecal samples [34]. ClpB will be assessed in serum and faecal samples by ELISA [Human Caseinolytic peptidase B protein homolog (CLPB) ELISA Kit (MyBioSource, San Diego, CA, USA)], according to manufacturer’s procedures.

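### A single p < 0.05 rule with no stated multiplicity control covers taxa at six ranks and 38 scalar secondary outcomes, so chance findings would be declared significant

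*Protocol article*

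**What the plan says.** The rule in Statistical analysis is "Differences will be considered statistically significant when" p is below 0.05. It is not limited to the primary outcomes, to one visit or to one class of variable. The same section sends continuous variables to one parametric or rank test according to their distribution, and it mentions no adjustment for multiple comparisons.

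The Secondary outcomes section asks for diversity, richness and "characterization of microbes at phylum, class, order, family, genus, and species level at baseline, and 3, 6, 9, and 12 months". The section on gut microbiota and metabolites adds that "Whole-metagenome shotgun sequencing will be performed on the Illumina HiSeq3000 platform". It refers to earlier work for the characterisation method and gives no separate significance rule for taxa.

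Secondary outcomes also lists scalar measures: metabolites, ClpB, inflammatory and permeability markers, glycaemic indices, lipids, vitamins and minerals, incretins and the gastrointestinal quality-of-life score. Study objectives names microbiota composition, the glycaemic indices, the metabolites with ClpB, and gastrointestinal quality of life as secondary aims. The inflammatory markers, lipids, micronutrients and incretins appear only under Secondary outcomes.

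**The concern.** The rule is stated, and it is applied to a very large set of comparisons. Shotgun sequencing resolved to species level can produce many taxa per sample, and the scalar list is long even without them. At 5% per test, chance results accumulate with the number of tests, and nothing in the published rule separates them from real effects.

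This matters because the Discussion wants to learn about mechanism, and looks ahead to a post-surgery protocol in which the gut microbiota is a therapeutic target. Taxa or markers declared significant by chance would feed directly into that argument.

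**Working it through.** The article gives no error rate for the secondary outcomes, so there is no figure of its own to reproduce. The check counts the tests and applies the stated threshold under no effect.

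**Inputs from the article**
- Threshold: 0.05 per test (Statistical analysis).
- Scalar outcomes (Secondary outcomes): 6 metabolites + 1 ClpB + 10 inflammatory and permeability markers + 5 glycaemic + 5 lipids + 8 vitamins and minerals + 2 incretins + 1 quality-of-life score = 38.
- Scalars that are also named aims (Study objectives): 5 glycaemic + 6 metabolites + 1 ClpB + 1 quality of life = 13.
- Visits after the start of the intervention at 3 months: 6, 9 and 12 months, so 3.

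The count of 38 is on the low side. It omits diversity and richness, and it counts the 6 metabolites and ClpB once although they are measured in both serum and faeces (38 + 7 = 45).

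**Assumptions, not in the article**
- Each taxon is compared between arms, with 100-300 testable species.
- Where several visits are counted, each scalar is tested separately at each visit.
- Correlations between outcomes are 0.2-0.5, and between visits 0.5-0.8.

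**Formulas.** Expected false positives = m × 0.05, whatever the correlation. Chance of at least one, if independent = 1 − 0.95^m. With correlation, the chance was found by simulating correlated test statistics.

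| Set | m | Expected false positives | At least one, independent | At least one, correlated |
|---|---|---|---|---|
| Scalars named as aims, one visit | 13 | 0.65 | 49% | not run |
| All scalars, one visit | 38 | 1.9 | 86% | 56-80% |
| All scalars, three visits | 38 × 3 = 114 | 5.7 | 99.7% | about 80-98% |
| Taxa, per 100 tested at one visit | 100 | 5 | 99.4% | not run |
| Taxa, 300 tested at one visit | 300 | 15 | about 100% | not run |

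For a larger set of 500 tests at one visit, the simulated chance of at least one false positive is 98.8% at correlation 0.5 and 73% at 0.7.

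**Does the effect-size rule filter these out?** The article also uses Cohen's d, with 0.50 as the mark of a medium effect. In an unpaired t-test with n per arm, significance needs |d| > t × √(2/n).
- At 29 per arm: 2.003 × √(2/29) = 0.53.
- At 22 per arm: 2.018 × √(2/22) = 0.61.

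At the planned size, any false positive from such a test therefore also passes the medium-effect mark, so the effect-size rule is no safeguard.

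**The case against.** The strongest reply is that 0.05 is only the customary level. The sentence does not say that p-values are unadjusted, and an adjusted p-value compared with 0.05 would satisfy it. Multiplicity for secondary and sequencing outcomes is often left to a statistical analysis plan, which is not shown here. It stands that the article never states that the tests are unadjusted. But the article is not silent: it publishes a threshold for differences with no exception, and someone following that text would apply it to every taxon and marker.

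Second, the article separates primary from secondary outcomes. Its Background and Discussion speak of exploring mechanisms, and no secondary result decides whether the trial succeeded. This stands and limits the gravity of the point. However, the exploratory wording is not carried into the outcome or analysis sections, where it would govern interpretation.

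Third, two stronger readings are tempting and are not supported.
- A reader might infer that false positives are almost guaranteed throughout. For the scalars at one visit this is too strong, given 86% under independence and less with correlation. Correlation is likely, since the three HOMA indices share one method. For taxa, and for the scalars over three visits, the statement depends on numbers and a testing scheme that the article does not give.
- A reader might infer that all 38 scalars are aims of the trial. Only 13 are; the other 25 are listed solely as secondary outcomes.

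Finally, one might confine secondary significance claims to 12 months. Capsules are taken between 3 and 6 months after surgery, so that would remove inference at the end-of-treatment visit. The article gives no ground for doing so.

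**Conclusion.** The point holds in limited form. As published, one threshold with no stated multiplicity control governs all differences. Under no effect it yields about 5 false declarations per 100 taxa tested per visit, and 1.9 among the 38 scalars at one visit. The taxon figure assumes taxon-by-taxon testing between arms, and the article gives no number of taxa. The expected scalar count needs no correlation assumption; the chance of at least one does (86% if independent, roughly 56-80% at correlations of 0.2-0.5).

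The trustworthiness of secondary conclusions is at stake; the analysis of the primary outcomes is not touched by this point. The change should be made, but the trial's validity does not depend on it.

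**What to change.** - Limit the flat p < 0.05 rule in Statistical analysis to the primary outcomes.
- For between-arm comparisons of taxa, declare significance only at a Benjamini-Hochberg false discovery rate of 5% within each rank at each tested visit.
- For the scalar secondary outcomes, report estimates with 95% confidence intervals at all visits. Either label them exploratory, or apply Benjamini-Hochberg across them at visits the investigators name in advance, which may include the 6-month end-of-treatment visit.

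Control then holds within each family. Six ranks at three visits make 18 families. If nothing is affected, about 18 × 0.05 = 0.9 families at most would show any declared taxon; at a single visit it would be 6 × 0.05 = 0.3. Naming few tested visits keeps this small.

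The cost is some wording, a line of analysis code and fewer nominally significant secondary results. No new data or participants are needed. The article reports 14 participants so far and blinding of researchers until completion, so at that stage the rule could be amended before any comparative result was known.
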